### Facial Neuromuscular Retraining

Mime therapy [8,9] and facial neuromuscular retraining (fNMR) [10] are 2 rehabilitation techniques for managing facial palsy sequelae that stand out in the literature [11]. Mime therapy consists of facial massage and specific facial retraining to coordinate both hemifaces by using emotional cues to express a particular facial movement or by starting to use a specific muscle to create an expression [8]. Similarly, fNMR consists of relearning motor patterns to improve facial movements through conscious, consistent, and slow selective activation of facial muscles using individualized training programs made by qualified facial therapists [12]. This therapy aims to normalize facial muscle functions by inhibiting synkinetic contractions and improving resting tone altered by contractures [13]. In the literature, these 2 therapies have recently merged into one called fNMR, which combines techniques such as soft tissue massage, biofeedback, education, relaxation, and selective movement retraining [14]. fNMR is considered a well-supported approach that has been studied in many cohort studies [14].

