### Recruitment and Compensation

As determined, thanks to a power calculation measure based on Martineau et al [22] to reach a power of 0.8 with a size effect of 0.6 and an α of .005, 90 patients with peripheral facial palsy of diverse etiologies in the paretic (n=30), early synkinetic (n=30), or chronic synkinetic phase (n=30) will be recruited to the study. They will then be randomized into 2 groups, mirror therapy plus fNMR or fNMR alone, by computerized block randomization. No compensation or incentive is planned to be provided at this time. Recruitment is planned to be conducted in 3 tertiary care centers (hospitals) in Canada, England, and Belgium (Hôpital Maisonneuve-Rosemont, Queen Victoria Hospital, and Sint-Augustinus GZA Hospital, respectively). A telehealth option will be available for the participants via institutionally secured platforms.

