### Study Procedures

This trial will compare the effect of mirror therapy in addition to gold standard fNMR (experimental group) over fNMR alone (control group) in patients with peripheral facial palsy dealing with sequelae 3-12 months after onset. During 6 therapy sessions (Textbox 1), all patients will benefit from standardized education on facial anatomy and physiology, eye care, and management of facial dysfunction (eg, eating, drinking, speaking, and nonverbal communication), as well as from rehabilitation to increase symmetry and decrease synkinesis, specific to their needs. These sessions will be provided by speech-language, physical, or occupational therapists, all certified by their respective professional corporation. In addition, a minimum of 5 years of expertise in facial palsy training is required to be included in the study. These clinicians will also perform the different study measurements, but 3 judges (also experts in facial therapy but blinded to therapy allocation) will then analyze the data. The mirror therapy group will also receive modified visual feedback during facial retraining, along with appropriate instructions about its use. In parallel, patients will be prescribed daily specific at-home rehabilitation depending on the nature of their group. Patients in the combined group (mirror therapy plus fNMR) will do their therapy at home with the MEPP 2.0 app [31], while patients in the fNMR group alone will do their therapy at home with the Physitrack app [32]. Figure 2 presents the overall study design.

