### Statistical Analysis

As mentioned, a power calculation was done based on a previous study [23] for the primary outcome (changes from baseline to 6 months). Every measure of facial symmetry and synkinesis will be judged by 3 assessors, blinded to group assignment. Intraclass correlation coefficients will be calculated to ensure interrater reliability, and the resulting means of the assessors’ findings will be used for further statistical analysis. We will first gather descriptive statistics to provide summary data. Then, for continuous variables (Emotrics measurements, Sunnybrook global score, FNGS 2.0 global scores, FACE score, FDI, and intrinsic motivation inventory), a mixed model analysis with patients as random variables and time+group assignment as fixed variables will be considered, with auto-regressive covariance structure, given the structure of the time points for the assessments. Comparison between the timing of recruitment after PFP onset (3-6 months after onset vs 6-9 months vs 9-12 months) and outcomes at T2 and T3 will be specifically measured using multilevel analysis. Kruskal-Wallis analyses will be considered for ordinal variables (synkinesis subscores, symmetry subscores, and motivation subscores). Finally, chi-square analysis will be considered for dichotomous variables (adherence yes or no). Data will be encoded with Excel sheets, and SPSS (IBM Corp) will probably be used for statistical analysis.

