### Strengths and Limitations

The primary strength of this protocol lies in its international multicentric collaboration, which will facilitate the examination of a substantial number of participants representing diverse etiologies of peripheral facial nerve palsy (n=90, with 45 patients per group). The randomized controlled trial design used in this study allows for assessing the potential additional benefits of incorporating mirror therapy into the rehabilitation of PFP. This investigation has the potential to contribute to an evidence-based approach for clinicians involved in the care of these patients.

However, the study design does have certain limitations. First, it is not feasible to blind both the patients and treating clinicians to the assigned conditions, which could introduce bias in terms of motivation and perception of treatment efficacy. To mitigate these risks, blinded judges will be involved in assessing participants, and therapists will use a standardized feedback approach in both therapy sessions and assessments. Additionally, using Emotrics will allow for more objective facial metrics at each assessment time point [33,45]. Second, the inclusion of paretic patients in the study poses a potential confounding factor due to the occurrence of spontaneous recovery in certain cases of facial palsy [3]. However, the large number of participants and their enrollment at least 3 months after the onset of symptoms should help mitigate potential biases. It is worth noting that in Bell palsy, the most common cause of PFP, approximately 70% of patients experience full recovery within 3 months of onset [3]. The advantage of including patients across such a broad timeframe (3-12 months after onset) is to recruit a cohort that is as representative as possible of the clinical reality of facial rehabilitation in different countries.

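### No stratification by centre is stated and the model has no centre term in a three-country trial of individualised therapy; the cost is precision, not validity

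*Protocol article*

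**What the plan says.** **Centres and allocation** (Recruitment and Compensation): "Recruitment is planned to be conducted in 3 tertiary care centers (hospitals) in Canada, England, and Belgium". On the method of allocation: "They will then be randomized into 2 groups, mirror therapy plus fNMR or fNMR alone, by computerized block randomization". Block size, strata and patients per centre are not given.

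**Model** (Statistical Analysis), for Emotrics, Sunnybrook, FNGS 2.0, FACE, FDI and the motivation inventory: "a mixed model analysis with patients as random variables and time+group assignment as fixed variables will be considered". Centre, country and therapist do not appear anywhere in the analysis text. A second analysis, of time since onset, says "outcomes at T2 and T3 will be specifically measured using multilevel analysis". Its levels are not named, and its stated purpose is the onset window, not the centre.

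**Sources of variation between centres.** The background on fNMR describes it as "using individualized training programs made by qualified facial therapists". Study Procedures says "These sessions will be provided by speech-language, physical, or occupational therapists, all certified by their respective professional corporation", and has the treating clinicians take the study measurements.

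**What limits that variation.** Three judges blinded to allocation score the recorded assessments, and their mean is analysed. Therapists must be experienced ("a minimum of 5 years of expertise in facial palsy training is required to be included in the study"), patient education is standardised, and Strengths and Limitations adds that "therapists will use a standardized feedback approach in both therapy sessions and assessments".

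**The concern.** Case mix, style of delivery and local recording of assessments can all differ between hospitals in three countries, and the therapy depends on the therapist. Centre is known at randomisation, so differences between centres can be balanced by design and removed in analysis at almost no cost. The article states neither step, and the model that it does specify leaves centre out.

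At stake is the precision of one arm comparison in 90 patients, planned at a power of 0.8. In the stated model any variation between centres falls into the between-patient variance. If the arms happen to be unevenly split within centres, part of the centre difference moves into the observed arm difference and nothing takes it out.

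**Working it through.** **Inputs from the article.** 90 patients, 45 per arm, three centres, effect size 0.6, power 0.8.

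**Assumptions.** 30 patients per centre (50/25/15 as an alternative), differences between centre means, and the share of variance due to centre. None of these is in the article, so each is shown over a range. Centre means are differences in the quantity analysed, in units of the within-centre SD. There is one value per patient and no dropout.

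**Significance level used.** The article prints α = .005. At that level, two-sided, an effect of 0.6 with power 0.8 needs 148 patients (normal) or 152 (t-test), not 90. At .05 two-sided the result is 88 or 90. The calculations below therefore use .05 two-sided, the level that reproduces 90. That discrepancy is a separate matter.

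**Reading A: blocks ignore centre.**

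1. Split within a centre. The number in the experimental arm among 30 is hypergeometric(90, 45, 30), with SD = √(30 × 0.5 × 0.5 × 60/89) = 2.25. A given centre splits 19:11 or worse with probability 0.117, and at least one of three does so with probability about 0.26. For 18:12 or worse in at least one centre the figure is about 0.50, and for 20:10 or worse about 0.11. With centres of 50/25/15, the chance of an arm difference of at least 6 in some centre is about 0.37, and of at least 10 about 0.06 to 0.07. Block size (4, 6, or a single block of 90) hardly matters.

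2. Shift in the arm difference. Its variance is S² × (1/45 + 1/45), where S² is the variance of the centre means over the 90 patients.
   - Means 0/0.5/1.0: S² = 0.1667 × 90/89 = 0.1685, so SD = √(0.1685 × 2/45) = 0.087. The simulated 95th percentile of the absolute shift is 0.178, and 0.178/0.6 = 30%. The centre share of variance is 0.1667/1.1667 = 14%.
   - Means 0/0.25/0.5: both figures halve. The SD is 0.043 and the 95th percentile 0.089, and 0.089/0.6 = 15%. The share is 0.0417/1.0417 = 4%.

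3. Size against ordinary sampling error. With within-centre SD 1 the standard error is √(2/45) = 0.211. Adding the shift gives √(0.211² + 0.043²) = 0.215 (about 2% larger) and √(0.211² + 0.087²) = 0.228 (about 8% larger).

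4. Power and type I error, simulated with 30 per centre and total SD 1:

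| Centre share of variance | Power, no strata, no centre term | Power, strata and centre term | Type I error, no strata, no centre term |
|---|---|---|---|
| 0 | 0.789 | 0.794 | 0.051 |
| 0.02 | 0.805 | 0.811 | 0.053 |
| 0.05 | 0.796 | 0.831 | 0.048 |
| 0.10 | 0.809 | 0.843 | 0.049 |
| 0.20 | 0.805 | 0.890 | 0.050 |

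The gain runs from about 0 to about 9 points (0.890 − 0.805 = 0.085). Type I error stays at its nominal level.

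**Reading B: blocks run within centre, but the model omits centre.** The true variance of the arm difference is then (1 − ρ) × 2/45, where ρ is the centre share, while the model estimates roughly 2/45. The effective critical value is 1.96/√(1 − ρ): 2.011, 2.066 and 2.191 for ρ = 0.05, 0.10 and 0.20. The two-sided errors are about 0.044, 0.039 and 0.028. Simulation gives 0.042, 0.042 and 0.029. The test is conservative.

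**The case against.** Most of the case on the other side stands, and it narrows the point.

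- A reader might infer that randomisation is known to be unstratified. The article does not say so. Blocks within centre fit its wording, and a condensed article commonly leaves strata and block size to the full protocol.
- A reader might infer that the therapist professions differ between countries. Three professions are permitted and none is tied to a country or centre.
- A reader might infer that a test which ignores centre is invalid because patients at one hospital are not independent. With individual randomisation it is not: there is no bias, and simulated type I error is 0.048 to 0.053. Chance imbalance and wider error are largely the same sampling variability, which the standard error already reflects.
- Local assessment matters less than it first appears, given the blinded judges, the averaging of their scores, automatic landmark placement in Emotrics, the experience minimum and the standardised feedback. How recordings are made locally could still vary.
- Centre means spanning a full SD are a severe assumption. The primary outcome is change from baseline to 6 months, so stable centre differences partly cancel and only differences in change count.

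It can also be said that the model is provisional and that covariates may be left to an analysis plan. This carries less weight. The article does list the model's terms, and that list is short of one on either reading of the allocation.

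**Conclusion.** The point holds as a matter of efficiency and of consistency between design and analysis. The stated model lacks a centre term in a three-hospital trial of individualised therapy, and stratification by centre is not stated. If blocks ignore centre, the loss is precision and an uncorrected chance shift, with a 95th percentile of about 0.09 to 0.18 SD over the two sets of centre means; the remedy gains 0 to about 9 points of power for a centre share of 0 to 0.20. If blocks run within centre, the type I error falls to about 0.04 at a 5 to 10% share and 0.03 at 20%.

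These sizes rest on assumed centre sizes and centre variation. With no centre variation the gain is nil. The upper figure, 30% of the planned effect, should not be read as an expected error. Priority is minor to moderate.

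**What to change.** - **Recruitment and Compensation:** state that allocation is by central computerised permuted blocks within centre. If this is already so, say it.
- **Statistical Analysis:** add centre as a fixed effect in the mixed models for the continuous outcomes. Three centres are too few to estimate a random centre effect reliably. If the arm effect is read as a difference in change over time, let centre also interact with time; otherwise only stable centre differences are removed.

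The main effect costs 2 degrees of freedom (a centre-by-time term would add more), and list management becomes slightly more complex. No extra patients are needed. The term does not reach the Kruskal-Wallis and chi-square outcomes, which would benefit only from the stratified allocation. The article describes ethics approval and inclusion as still to come, so on its own timetable both changes can be made before enrolment.

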### Study Procedures

This trial will compare the effect of mirror therapy in addition to gold standard fNMR (experimental group) over fNMR alone (control group) in patients with peripheral facial palsy dealing with sequelae 3-12 months after onset. During 6 therapy sessions (Textbox 1), all patients will benefit from standardized education on facial anatomy and physiology, eye care, and management of facial dysfunction (eg, eating, drinking, speaking, and nonverbal communication), as well as from rehabilitation to increase symmetry and decrease synkinesis, specific to their needs. These sessions will be provided by speech-language, physical, or occupational therapists, all certified by their respective professional corporation. In addition, a minimum of 5 years of expertise in facial palsy training is required to be included in the study. These clinicians will also perform the different study measurements, but 3 judges (also experts in facial therapy but blinded to therapy allocation) will then analyze the data. The mirror therapy group will also receive modified visual feedback during facial retraining, along with appropriate instructions about its use. In parallel, patients will be prescribed daily specific at-home rehabilitation depending on the nature of their group. Patients in the combined group (mirror therapy plus fNMR) will do their therapy at home with the MEPP 2.0 app [31], while patients in the fNMR group alone will do their therapy at home with the Physitrack app [32]. Figure 2 presents the overall study design.

**Figure 2 figure2:**
[figure not shown]
Overall study design. Participants in the control group and in the experimental group are assessed at baseline (T0), 3 months postintervention (T1), 6 months postintervention (T2), and 12 months postintervention (T3). fNMR: facial neuromuscular retraining.

Frequency and length of appointment.SessionsSession 1 (1 hour to 1 hour and 30 minutes) for initial assessment and start of management.Session 2 (1 hour) 1 month after session 1.Session 3 (1 hour) 1 month after session 2.Session 4 (1 hour) generally 1-2 months after session 3.Session 5 (1 hour) is generally 3 months after session 4.Session 6 (1 hour) final session generally 6 months after session 5, then discharge to continue independently.The total treatment course will last 12 months.2-3 sessions of 10 to 15 minutes of daily home rehabilitation are expected to be done by the patients from baseline until 12 months.

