**Methods:**

This study is a randomized controlled trial that compares the effect of fNMR combined with mirror therapy (experimental group: n=45) with fNMR alone (control group: n=45) in 90 patients with peripheral facial palsy presenting with sequelae 3-12 months after onset. Both groups will receive 6 months of rehabilitation training. Facial symmetry and synkinesis; participants’ quality of life; and their psychological factors, motivation, and compliance will be assessed at baseline (T0), 3 months (T1), 6 months (T2), and 12 months (T3) postintervention. Outcome measures are (1) changes in facial symmetry and synkinesis assessed with facial grading tools, (2) quality of life changes with patient questionnaires, and (3) therapy motivation with a standardized scale, as well as adherence to treatment with metadata. Changes in facial symmetry and synkinesis will be judged by 3 assessors blinded to group assignment. Mixed models and Kruskal-Wallis, chi-square, and multilevel analyses will be conducted according to the appropriate variable type.

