### Measures

For data collection, each measure will be taken at baseline, 3 months, 6 months, and 1-year postintervention. Evaluation sessions will be recorded, allowing 3 independent evaluators to blindly assess the objective outcome measures. The final assessment (T3) will measure the training retention of participants following therapy sessions.

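### Treatment length is given as both 6 and 12 months and the visits are labelled postintervention; counted from baseline, as the primary outcome implies, T3 cannot measure retention

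*Protocol article*

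**What the plan says.** **Duration.** The abstract (Methods) states: "Both groups will receive 6 months of rehabilitation training". Textbox 1, under Study Procedures, states: "The total treatment course will last 12 months". It describes session 6 as the "final session generally 6 months after session 5, then discharge to continue independently" and adds that sessions of "daily home rehabilitation are expected to be done by the patients from baseline until 12 months".

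**Visit timing.** In the abstract, outcomes are "assessed at baseline (T0), 3 months (T1), 6 months (T2), and 12 months (T3) postintervention". The Figure 2 legend attaches the label to each visit in turn: "3 months postintervention (T1), 6 months postintervention (T2), and 12 months postintervention (T3". The Measures section says "each measure will be taken at baseline, 3 months, 6 months, and 1-year postintervention".

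**Primary outcome.** The Statistical Analysis section describes it as the change between baseline and 6 months.

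**Purpose of T3.** The Measures section says: "The final assessment (T3) will measure the training retention of participants following therapy sessions".

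**The concern.** These statements cannot all be true. A 6-month course and a 12-month course are different treatments. A visit 6 months after the intervention ends is also not a visit 6 months after baseline, whichever duration is right.

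The anchor decides what is estimated. Counted from baseline, the primary comparison is an on-treatment effect and T3 is an end-of-course effect. Counted from the end of treatment, both are off-treatment effects. A reader relying on the abstract and the Measures section would take T2 as end of treatment and T3 as durability. Textbox 1 supports neither.

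There are practical consequences too. Three centres working from this text could schedule the primary visit at different times. Adherence is judged against the prescribed programme, whose length is in doubt. The article itself names spontaneous recovery in paretic patients as a confounder, so time since baseline matters when interpreting T2.

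**Working it through.** **1. Reproduce the 12-month figure.** Adding the gaps in Textbox 1, with session 1 at month 0:

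- Session 2: 0 + 1 = month 1
- Session 3: 1 + 1 = month 2
- Session 4: 2 + (1 or 2) = month 3 or 4
- Session 5: + 3 = month 6 or 7
- Session 6: + 6 = month 12 or 13

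This reproduces the stated 12 months (13 if session 4 is late) and agrees with home training to month 12. It cannot be reconciled with 6 months.

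**2. Place the visits under each reading** (months from baseline):

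| Time origin | T1 | T2 | T3 |
|---|---|---|---|
| Baseline | 3 | 6 | 12 |
| End of a 6-month course | 6+3 = 9 | 6+6 = 12 | 6+12 = 18 |
| End of a 12-month course | 12+3 = 15 | 12+6 = 18 | 12+12 = 24 |

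**3. Compare with the sessions.** From baseline, T1, T2 and T3 (3, 6, 12) sit at or within about a month of sessions 4, 5 and 6 (3–4, 6–7, 12–13). Under the other two readings no visit falls at month 6 from baseline, so a 6-month change counted from baseline could not be measured.

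**4. Compare with the calendar.** Inclusion is to end in 2027 and the last T3 is to fall in 2028. For a last patient enrolled in any month of 2027:

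- T3 at +12 months: January–December 2028, so 12 of 12 enrolment months fit.
- T3 at +18 months: July 2028–June 2029, so 6 of 12 fit (January–June enrolment).
- T3 at +24 months: January–December 2029, so 0 of 12 fit.

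The Results section says inclusion starts in late 2024 and runs 3 years. If that means enrolment closes in October–December 2027 (an assumption), the +18 reading puts the last T3 in April–June 2029. The calendar supports the baseline anchor and rules out the 12+12 reading. It does not on its own rule out 6+12.

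**5. What T2 and T3 are, counted from baseline.**

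- Sessions delivered by month 6: 5 if session 5 is at month 6, 4 if it is at month 7. T2 is on treatment.
- T3 minus session 6: 12 − 12 = 0, or 12 − 13 = −1 month. T3 is at the last session or one month before it.
- Training-free interval before T3: 12 − 12 = 0 months, because home training is prescribed to month 12.

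**6. Home training between T2 and T3.** Reading Textbox 1 as 2–3 sessions a day of 10–15 minutes gives 2×10 = 20 to 3×15 = 45 minutes a day. Over 6 months (182.6 days): 182.6×20/60 = 60.9 h to 182.6×45/60 = 137.0 h. That is half of the 121.8–273.9 h prescribed over 12 months.

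**The case against.** The 6-versus-12 conflict is hard to dispute. The case against the rest has four parts.

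*The Statistical Analysis section may not fix the clock.* Baseline there may only name the comparator visit, and 6 months may only be the name of T2. That is a fair reading of the phrase. It leaves the anchor undefined, however, so the primary visit still has three possible dates.

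*The label may not apply to every visit.* In the abstract and the Measures section the word closes a list and could attach only to the last item. That is true of those two places, but the Figure 2 legend attaches it to T1, T2 and T3 separately.

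*Retention could mean gains held without a therapist.* Counted from baseline, session 5 is at month 6–7, so T3 at month 12 follows 5–6 months without therapist contact. That interval is real and is the point most favourable to the plan. It does not make T3 an assessment after the therapy sessions: Textbox 1 names session 6, at month 12–13, as the final one, and daily training is prescribed throughout the interval.

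*The 6+12 reading gives a true retention visit.* With T3 at month 18, it would come 5–6 months after session 6 and 6 months after home training ends. But that reading starts the clock at the end of a 6-month course that Textbox 1 contradicts, and it puts T2 at month 12. It fits the calendar only if the last patient enters by June 2027.

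**Conclusion.** The concern holds. The two durations contradict each other, and the schedule supports 12 months. The visit labels leave the primary time point at month 6, 12 or 18 from baseline. On the best-supported reading, counted from baseline, T2 is an on-treatment assessment after 4 or 5 of 6 sessions, and T3 has no training-free interval before it, so the retention claim fails.

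The conclusion about T3 depends on the baseline anchor. That anchor rests mainly on the match between visits and sessions and on the wording of the primary outcome; the calendar is supporting evidence only. Textbox 1 gives the later session intervals as typical rather than fixed, but drift of that kind cannot turn a 12-month course into a 6-month one. Because both arms share one schedule, the between-arm comparison is not biased by this. The harm lies in what T2 and T3 can be said to show and in the risk of inconsistent scheduling. It should be fixed before the trial relies on these visits.

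**What to change.** - State one treatment duration throughout: 12 months, as in Textbox 1, unless the schedule itself is changed. Correct the abstract accordingly.
- In the abstract, the Figure 2 legend and the Measures section, replace the postintervention label with months from baseline (or from randomization, if that is the intended origin).
- In the Statistical Analysis section, name T2 at month 6 from baseline as the primary time point and say that it is on treatment.
- Relabel T3 as an end-of-course assessment and remove the retention statement from the Measures section. Keep that statement only if sessions and prescribed home training are both confirmed to end before T3.

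The cost is wording. The article says ethics approval was still to be sought, by January 2024; if it has since been granted, the same changes would need an amendment. Keeping a genuine retention visit would cost more, because sessions and home training would have to be rescheduled to end before T3.
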